### **5.3 General Concomitant Medication and Supportive Care Guidelines**

Because there is a potential for interaction of Vinorelbine and Erlotinib with other concomitantly administered drugs through the cytochrome P450 system, the case report form must capture the concurrent use of all other drugs, over-the-counter medications, or alternative therapies. The Principal Investigator should be alerted if the patient is taking any agent known to affect or with the potential to affect selected CYP450 isoenzymes.

### **5.4 Duration of Therapy**

In the absence of treatment delays due to adverse events, treatment may continue indefinitely or until one of the following criteria applies:

- Disease progression,
- Intercurrent illness that prevents further administration of treatment,
- Unacceptable adverse event(s),
- Patient decides to withdraw from the study, or
- General or specific changes in the patient's condition render the patient unacceptable for further treatment in the judgment of the investigator.

### **5.5 Duration of Follow Up**

Patients will be followed every 3 monthly for 52 weeks after removal from study or until death, whichever occurs first. Patients removed from study for unacceptable adverse events will be followed until resolution or stabilization of the adverse event.

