### 1.2 Secondary Objectives

- To assess for pharmacokinetic interaction of erlotinib on navelbine
- To assess the usefulness of circulating endothelial cells (CECs) and circulating endothelial progenitor cells (CEPs) as surrogate biomarkers to determine optimal anti-angiogenic effect of treatment
- To evaluate the clinical benefit rate (CR+PR+SD) and overall survival

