### **5.6 Criteria for Removal from Study**

Patients will be removed from study when any of the criteria listed in Section 5.4 applies. The reason for study removal and the date the patient was removed must be documented in the Case Report Form.

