#### 11.1.6 Overall Survival

The duration of overall survival will be calculated from the date of registration to the date of death.

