## **13.1 Analysis**

- The primary aim of this study is to determine the dose limiting toxicities of oral vinorelbine combined with erlotinib and the maximal tolerated dose (MTD) of this drug combination in patients with non-small cell lung cancer. The toxicity profile will be graded as described above and reported with the corresponding dose level.
- The MTD will be dose at which less than 2 DLTs occur. Steady state plasma drug

concentrations, area under the curve values, volume of distribution and clearance of oral vinorelbine and erlotinib in each patient will be calculated and correlated with dose. These quantities will be summarized for all patients.

- Response rates (Complete response, partial response, stable disease) to study treatment will be described based on RECIST criteria and summarized by dose. Overall survival will be measured from registration to death and analyzed by the Kaplan-Meier method.
- Exploratory analysis of known functional SNPs in the transporter genes will be described in relation to dose and response. An exploratory analysis of the changes on CEC/CEP assessment of angiogenesis in each group would be performed.

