### 13.2 Sample size considerations:

As this is a phase 1 study, no formal sample size calculation is possible. The number of patients accrued will depend on the DLT reached on each arm of the study. Between 3-6 patients will be observed on each dose levels and an expanded cohort of 6 patients will be observed on the MTD. The anticipated accrual to this study is between 12 (if there are at least 2 DLT at dose level 1 and DLT at level -1) to 78 patients (if dose level 5 is reached and the cohort receiving erlotinib 150 mg is included).

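### Survival follow-up ends 52 weeks after removal from study, so censoring after one year depends on time to progression and the later Kaplan-Meier curve may be biased, probably upward

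*Protocol*

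**What the plan says.** The relevant statements are spread over six sections of the protocol.

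- Section 1.2 makes survival a secondary objective: "To evaluate the clinical benefit rate (CR+PR+SD) and overall survival".
- Section 5.4 sets no time limit on treatment: "treatment may continue indefinitely or until one of the following criteria applies". The first criterion listed is "Disease progression". The others are intercurrent illness, unacceptable adverse events, patient withdrawal and deterioration in the investigator's judgement.
- Section 5.6 links these to leaving the study: "Patients will be removed from study when any of the criteria listed in Section 5.4 applies".
- Section 5.5 sets the length of follow-up from that point: "Patients will be followed every 3 monthly for 52 weeks after removal from study or until death, whichever occurs first".
- Section 11.1.6 defines the endpoint: "The duration of overall survival will be calculated from the date of registration to the date of death".
- Section 13.1 gives the analysis: "Overall survival will be measured from registration to death and analyzed by the Kaplan-Meier method". It names no landmark time, comparison or test.

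No section provides survival contact beyond 52 weeks after removal, a common cut-off date, or a censoring rule.

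**The concern.** Follow-up is anchored to an outcome, not to entry or a calendar date. A survivor removed at week 6 is censored at week 58 (6 + 52). One removed at week 60 is followed to week 112 (60 + 52). After week 52 the risk set therefore loses survivors in the order in which they left treatment, and leaving treatment is usually progression. Those who remain are still on study or recently removed, and they stand in for patients who progressed long before.

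At stake is the part of the survival curve beyond one year, and the median if it lies there. A confidence interval would not show the error, and pooling more patients would not shrink it.

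**Working it through.** **No figure to reproduce.** The protocol states no survival rate, event count or power for survival. The check asks what the follow-up rule does to the Kaplan-Meier estimate.

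**Inputs from the protocol.** Censoring time C = R + 52 weeks, where R is time to removal (5.4 to 5.6). Survival is estimated by Kaplan-Meier from registration (11.1.6, 13.1). At most 78 patients enter (13.2).

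**Assumed inputs.** Median R of 10 to 30 weeks and median post-removal survival of 20 to 52 weeks. Only one value has an anchor: Section 2.3 reports a 19-week median treatment duration, corresponding to time to progression, for single-agent metronomic vinorelbine in mixed refractory tumours. That is a proxy, not this regimen.

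**Step 1: up to week 52.** R cannot be negative, so C is at least 52 weeks. The rule censors nobody earlier, and the bias at week 52 is 0.0 in every scenario.

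**Step 2: mechanism, by hand.** Take exponential R (median 15 weeks) and independent exponential post-removal survival (median 26 weeks, hazard λ). Deaths occur only after removal. At t = 104:

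- Still on study: 2^(−104/15) = 0.0082.
- Alive: (26/11) × 2^(−104/26) − (15/11) × 2^(−104/15) = 0.1477 − 0.0112 = 0.137.
- Removed in weeks 52 to 104 and alive: (26/11) × 0.0625 × (2^(−1.467) − 2^(−2.933)) = 0.1477 × (0.3618 − 0.1309) = 0.0341.
- Kaplan-Meier risk set: 0.0082 + 0.0341 = 0.0423.

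With complete follow-up the hazard at week 104 is λ × (0.1366 − 0.0082)/0.1366 = 0.94λ. In the remaining risk set it is λ × 0.0341/0.0423 = 0.81λ. The estimated curve therefore falls too slowly. By simulation it reads 15.2% at week 104 against a true 13.7%.

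**Step 3: other assumptions.** Simulation of 400,000 patients per row, survival = R + post-removal survival. Entries are Kaplan-Meier minus truth, in percentage points.

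| Post-removal hazard | Medians (removal/post-removal, weeks) | Week 78 | Week 104 |
|---|---|---|---|
| Constant, independent of R | 10/20 | +0.3 | +0.5 |
| Constant, independent of R | 15/26 | +0.9 | +1.6 |
| Constant, independent of R | 13/39 | +0.7 | +1.3 |
| Constant, independent of R | 26/39 | +1.4 | +3.5 |
| Early removal predicts worse survival (shared gamma frailty, variance 0.5) | 13/26 | +2.0 | +4.8 |
| Same, variance 1 | 13/26 | +2.1 | +5.1 |
| Rising (Weibull shape 1.5), independent | 13/26 | +1.9 | +2.4 |
| Falling (post-removal frailty, variance 1), independent | 13/26 | −1.1 | −3.3 |
| Same, variance 2 | 13/26 | −1.5 | −5.0 |
| Falling (Weibull shape 0.6), independent | 13/26 | −1.0 | −2.5 |
| Same | 26/39 | −0.1 | −0.6 |

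In the frailty rows the medians are those at frailty 1, so the population medians are longer.

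A wider grid crossed removal medians of 13, 19 and 30 weeks with post-removal medians of 26, 39 and 52 weeks. At 104 weeks it gives +1.2 to +3.8 points with independence and +3.5 to +6.7 with shared frailty of variance 0.5. About 25% to 55% of patients are censored by the rule in that grid.

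**Step 4: the median.** With 15/26 the true median is 48.8 weeks, before the rule acts. With 26/39 independent it is 78.0 weeks; the Kaplan-Meier curve is 51.4% at week 78 and 44.3% at week 91. Linear interpolation puts the estimated median (51.4 − 50)/(51.4 − 44.3) × 13 = 2.6 weeks late.

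**Step 5: random error.** SE = √(p(1 − p)/n). With all 78 patients pooled and fully followed: √(0.3 × 0.7/78) = 5.2 points and √(0.2 × 0.8/78) = 4.5 points. With 20 patients: 10.2 and 8.9 points.

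**The case against.** **Direction.** A reader might infer that the curve must be biased upward. The documents do not support that. They give no post-removal survival data, and the falling-hazard rows show a downward bias. The upward reading needs a constant or rising post-removal hazard, or early progression that predicts worse later survival. The last is the usual expectation, which is why upward is the more likely direction, but it remains an assumption. This part of the objection stands.

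**Model.** Letting nobody die on study exaggerates the contrast in the risk set. If 15% of removals are deaths (assumption), the excess at 104 weeks for 19/39 independent falls from 2.6 to 1.8 points. The frailty results also describe a longer-surviving population: variance 0.5 moves medians of 19 and 39 weeks to about 22.7 and 46.6. With the medians held at 19 and 39 the true 104-week survival is 35.1% and the bias stays near 5 points. The sizes are therefore rough; the mechanism is not in doubt.

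**Importance.** Survival here is secondary and descriptive, spread over two schedules and several dose levels, and no stated decision depends on it. That stands and keeps the point minor.

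**A separate plan could settle it.** A statistical analysis plan could restrict reporting to 52 weeks. It could not recover follow-up that the protocol never collected.

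**Time origin.** A reader might also infer that survival has no defined start, because Section 4 marks registration procedures as not applicable. That shows only that no procedure is described, not that no date is recorded; Section 12.2 relies on enrolment. It forms no part of this point.

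**Conclusion.** The point holds as a minor design weakness. Sections 5.4 to 5.6 make the survival censoring time depend on time to removal, so Kaplan-Meier censoring after week 52 is informative by construction. That much needs no assumption beyond a link between time to removal and later risk of death.

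The size and sign do rest on assumptions. At 104 weeks the distortion is about 1 to 7 points upward under the more likely patterns (0.5 with the shortest medians tried), and up to about 5 points downward if the post-removal hazard falls and is unrelated to time to removal. Against a standard error of 4.5 to 5.2 points with all 78 patients, and twice that with 20, the bias is broadly at or below random error. Survival up to 52 weeks, a median below 52 weeks and the MTD objective are unaffected.

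**What to change.** In Section 5.5, follow every patient for survival status, using the existing 3-monthly contact, until death or one common calendar cut-off that does not depend on the removal date, for example 52 weeks after the last patient's entry. In Section 13.1, state that patients alive at the cut-off are censored there. This removes the bias caused by the rule. Censoring would then follow entry date, which in a dose-escalation trial goes with dose level; say so wherever the curve pools levels.

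If follow-up cannot be extended, state in Section 13.1 that Kaplan-Meier survival is reported only to 52 weeks.

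The first option costs wording plus survival-status contacts for patients alive 52 weeks after removal. At 25% to 55% of 78 that is 0.25 × 78 = 19.5 to 0.55 × 78 = 42.9, about 20 to 43 patients at full accrual, limited by the cut-off. The second costs no extra contacts but gives up the curve beyond one year.

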### **5.6 Criteria for Removal from Study**

Patients will be removed from study when any of the criteria listed in Section 5.4 applies. The reason for study removal and the date the patient was removed must be documented in the Case Report Form.

## 6. DOSING DELAYS/DOSE MODIFICATIONS

If patient should encounter significant toxicity in the first cycle of treatment, treatment will be delayed until the recovery of the toxicity. Any delay beyond 2 weeks will result in removal from trial. The subsequent cycle will be started at the next lower dose level (see table).

In addition, the occurrence of a clinically significant toxicity that deemed related to either vinorelbine or erlotinib, in view of safety of the patient, that study drug can be discontinued. Patient will be allowed to continue in the trial with single agent therapy.

| Dose Level | Vinorelbine Dose
(Conventional Schedule) | Vinorelbine Dose (Metronomic
Schedule) |
|-------------------|-----------------------------------------------------|---------------------------------------------------|
| -1                | 30 mg/m^2, D1,D8 schedule          | 80 mg/week, D1,3,5 every 7 days            |
| 1                 | 40 mg/m^2, D1,D8 schedule          | 100 mg/week, D1,3,5 every 7 days           |
| 2                 | 50 mg/m^2, D1,D8 schedule          | 120 mg/week, D1,3,5 every 7 days           |
| 3                 | 60 mg/m^2, D1,D8 schedule          | 140 mg/week, D1,3,5 every 7 days           |
| 4                 | 70 mg/m^2, D1,D8 schedule          | 160 mg/week, D1,3,5 every 7 days           |
| 5                 | 80 mg/m^2, D1,D8 schedule          | 180 mg/week, D1,3,5 every 7 days           |
| Dose Level | Erlotinib Dose                               | Erlotinib Dose                             |
| 1                 | 100 mg, daily schedule                       | 100 mg, daily schedule                     |
| 2                 | 150 mg, daily schedule                       | 150 mg, daily schedule                     |

## 7. ADVERSE EVENTS: LIST AND REPORTING REQUIREMENTS

Adverse event (AE) monitoring and reporting is a routine part of every clinical trial.

### 7.1 Adverse Event Characteristics

- **CTCAE term (AE description) and grade:** The descriptions and grading scales found in the revised NCI Common Terminology Criteria for Adverse Events (CTCAE) version 3.0 will be utilized for AE reporting. All appropriate treatment areas should have access to a copy of the CTCAE version 3.0. A copy of the CTCAE version 3.0 can be downloaded from the CTEP web site (<http://ctep.cancer.gov>).
- **‘Expectedness’:** AEs can be ‘Unexpected’ or ‘Expected’ (see Section 7.1 above)

for expedited reporting purposes only. ‘Expected’ AEs (the ASael) are ***bold and italicized*** in the CAEPR (Section 7.1.1).

- **Attribution** of the AE:
  - Definite – The AE *is clearly related* to the study treatment.
  - Probable – The AE *is likely related* to the study treatment.
  - Possible – The AE *may be related* to the study treatment.
  - Unlikely – The AE *is doubtfully related* to the study treatment.
  - Unrelated – The AE *is clearly NOT related* to the study treatment.

## 7.2 Expedited Adverse Event Reporting

7.2.1 Expedited AE reporting for this study is required to the IRB.

7.2.2 Serious adverse events has to be reported to the sponsor or regulatory bodies and the Ethics Committee in accordance to the ICH guidelines.

All SAEs that are unexpected and related to the study drug will be reported. The investigator is responsible for informing HSA no later than 15 calendar days after first knowledge that the case qualifies for expedited reporting. Follow-information will be actively sought and submitted as it becomes available. For fatal or life-threatening cases, HSA will be notified as soon as possible but no later than 7 calendar days after first knowledge that a case qualifies, followed by a complete report within 8 additional calendar days.

Withdrawal from the study and therapeutic measures shall be at the discretion of the investigator. All adverse effects, regardless of severity, will be followed by the investigator until satisfactory resolution.

## 7.3 Routine Adverse Event Reporting

All Adverse Events **must** be reported in routine study data submissions.

## 7.4 Secondary AML/MDS

Investigators are required to report cases of secondary AML/MDS occurring on or following treatment to IRB

# 8. PHARMACEUTICAL INFORMATION

A list of the adverse events and potential risks associated with the investigational or commercial agents administered in this study can be found in Section 2.

## 8.1 Oral Vinorelbine

Oral Vinorelbine is manufactured by Pierre-Fabre and supplied locally by Orient

Euopharma as NAVELBINE® soft capsules 20 mg and 30 mg. The capsules also contains the following excipients: ethanol, water - purified, glycerol, macrogol 400, gelatin, sorbitol, sorbitan, medium-chain triglycerides, phosphatidyl choline, glycerides, hypromellose, propylene glycol, edible printing ink E120, titanium dioxide, iron oxide yellow CI77492 and / or iron oxide red CI77491.

Oral vinorelbine has been developed as a line extension of the IV dosage form. An oral dose of 80 mg/m^2 was demonstrated to correspond to 30 mg/m^2 of the IV formulation and 60 mg/m^2 orally to 25 mg/m^2 given by the IV route.

### **Presentation**

20 mg soft capsule: light brown soft capsule printed N20,  
30 mg soft capsule: pink soft capsule printed N30,  
Pack size: 1 capsule

### **Shelf life**

Store at 2 to 8° C (Refrigerate. Do not freeze) in the original container.  
Protect from light.

## **8.2 Erlotinib**

The 100 mg and 150 mg strengths are supplied as white film-coated tablets for daily oral administration.

TARCEVA (erlotinib) Tablets, 100 mg: Round, biconvex face and straight sides, white film-coated, printed in gray with "T" and "100" on one side and plain on the other side. Supplied in bottles of 30 tablets (NDC 50242-063-01).

TARCEVA (erlotinib) Tablets, 150 mg: Round, biconvex face and straight sides, white film-coated, printed in maroon with "T" and "150" on one side and plain on the other side. Supplied in bottles of 30 tablets (NDC 50242-064-01).

Store at 25°C (77°F); excursions permitted to 15°-30°C (59°-86°F).

## **9. CORRELATIVE/SPECIAL STUDIES**

### **9.1 Rationale for studying pharmacokinetics of oral vinorelbine and erlotinib in relation to CEC/CEP assays as a pharmacodynamic indicators of anti-angiogenesis**

Oral vinorelbine is a classic cytotoxic and Erlotinib is a specific oral TK-I of EGFR. Metronomic dosing of chemotherapy using low chronic doses has been suggested as a possible way of inducing an anti-angiogenic effect using classical cytotoxics.

This study will therefore utilize CEC/CEP assays as a pharmacodynamic endpoints to examine both dosing schedules and help determine if metronomic scheduling of vinorelbine has an anti-angiogenic effect. The clinical pharmacokinetics of oral vinorelbine and erlotinib may also have a bearing on the clinical outcome. The ethnic variability of drug pharmacokinetics is well described for several chemotherapeutic

agents. This is usually related to polymorphic differences across ethnic groups in the way drugs are absorbed, metabolized, distributed and eliminated. Given the paucity of data for this drug and its potential for drug interaction because of its effect of cytochrome p450 enzymes, we therefore propose to study the clinical PK of both drugs in Asian patients in conjunction with a pharmacodynamic study involving the use of CEC/CEP. This will also account for interpatient variability in pharmacokinetics of this drug and allow more accurate interpretation of the pharmacodynamic endpoints. Informed consent for the pharmacokinetic study will be obtained from patients with NSCLC who are planned to start treatment with as in the main study.

#### 9.1.1 CEC/CEP assays

Evaluation of CECs and CEPs will be carried out on blood collected at baseline and before each subsequent cycle of treatment (three weeks being defined as one cycle of treatment for both studies) and at time of documented clinical/radiological progression. The endothelial cells will be enumerated using four-colour flow cytometry. Colour-gated Flow Cytometry for the detection of Circulating Endothelial Progenitor Cells (CEPs):

3.5 milliliters of peripheral blood will be collected in ethylenediaminetetraacetic acid (EDTA) tubes through 21G needles. Anti-CD45 will be used to exclude hematopoietic cells; anti-CD31, -CD34, -CD105, -CD106, -CD133, and -P1H will be used to enumerate resting and activated circulating endothelial cells (CECs) and circulating endothelial progenitor cells (CEPs) using appropriate analysis gates. Monoclonal antibodies will be conjugated with fluorescein isothiocyanate (FITC), Rphycoerythrin (PE), peridinin chlorophyll protein (PerCP), or allophycocyanin (APC) as appropriate and availability. Cell suspensions after staining will be evaluated by a BD FACS Canto™ II flow cytometer.

Resting CECs is defined as negative for hematopoietic marker CD45; positive for endothelial markers P1H12, CD31, and CD34; negative for activation markers CD105 and CD106; and negative for the progenitor marker CD133.

Activated CECs is defined as CD45+, P1H12+, CD31+, CD34+, CD105+ or CD106+, and CD133.

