|                                                                                                     | 30                                                                  | 80                                                   | Level -1   |
|                                                                                                     | 40                                                                  | 100                                                  | Level 1    |
|                                                                                                     | 50                                                                  | 120                                                  | Level 2    |
|                                                                                                     | 60                                                                  | 140                                                  | Level 3    |
|                                                                                                     | 70                                                                  | 160                                                  | Level 4    |
|                                                                                                     | 80                                                                  | 180                                                  | Level 5    |
| Erlotinib
150 mg
(only in the
absence of DLT at
dose level 5 of
vinorelbine) | No DLT at dose level
5 of vinorelbine
(80 mg/m  ) | No DLT at dose level
5 of vinorelbine
(180 mg) |            |

Escalation of Erlotinib dose to 150 mg OM will only start if level 5 oral vinorelbine is reached without dose-limiting toxicities with Erlotinib 100 mg OM in each schedule.

The optimal anti-angiogenic dose of oral vinorelbine given in metronomic schedule will be determined from the Circulating Endothelial Cells/Circulating Endothelial Progenitors (CEC/CEP) assays correlations.

Efficacy will be assessed every 2 cycles during maintenance treatment. Each cycle will last 21 days with a window period of 7 days. Patients on the conventional schedule of vinorelbine who respond or have stable disease, vinorelbine will be stopped after 6 cycles and erlotinib continued. Patients on the metronomic schedule of vinorelbine who respond will continue on both vinorelbine and erlotinib.

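### Section 9.1.1 defines activated CECs as CD45-positive although CD45 is its own exclusion marker, so the activated-CEC count is not valid as written

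*Protocol*

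**What the plan says.** Protocol section 9.1.1 describes four-colour flow cytometry on blood taken at baseline, before each later cycle and at progression. Three of its statements concern CD45:

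- The exclusion step: "Anti-CD45 will be used to exclude hematopoietic cells". The same sentence goes on to assign the other antibodies to counting resting and activated CECs and the progenitor cells (CEPs).
- The resting population: "Resting CECs is defined as negative for hematopoietic marker CD45". It must also be positive for P1H12, CD31 and CD34, "negative for activation markers CD105 and CD106", and negative for CD133.
- The activated population: "Activated CECs is defined as CD45" with a plus sign. With the markers that follow, the line reads "Activated CECs is defined as CD45 + , P1H12 + , CD31 + , CD34", the last also with a plus, followed by "CD105 + or CD106 + , and CD133" with a minus on CD133.

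The assay has two stated uses. Section 1.2 lists as a secondary objective "To assess the usefulness of circulating endothelial cells (CECs) and circulating endothelial progenitor cells (CEPs) as surrogate biomarkers". Section 5.1 says "The optimal anti-angiogenic dose of oral vinorelbine given in metronomic schedule will be determined from the Circulating Endothelial Cells/Circulating Endothelial Progenitors" assay correlations. Section 13.1 describes the analysis of CEC/CEP changes as exploratory.

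**The concern.** The activated definition puts a plus on the marker that the same section uses to throw cells out. Nothing in the protocol explains why CD45 should change sign between resting and activated cells: the markers named as marking activation are CD105 and CD106 only. No other section corrects the sign.

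Section 9.1.1 spells out a full marker profile for two populations, resting and activated CECs, and one of the two is contradictory. If the laboratory follows the written profile, the activated-CEC series is either empty or made up of cells that the protocol itself labels haematopoietic. That series is part of the evidence for the biomarker objective and for the choice of an anti-angiogenic dose on the metronomic schedule.

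**Working it through.** No figure in the protocol is at issue and no formula applies. The check compares the definitions in section 9.1.1 marker by marker.

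| Marker | Exclusion step | Resting CEC | Activated CEC as written | Does the protocol explain the difference between resting and activated? |
|---|---|---|---|---|
| CD45 | positive cells removed | negative | positive | No |
| P1H12, CD31, CD34 | – | positive | positive | No difference |
| CD105, CD106 | – | both negative | at least one positive | Yes, named as activation markers |
| CD133 | – | negative | negative | No difference |

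The consequences follow in four steps.

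1. **Exclusion applied first.** Only CD45-negative cells remain. The activated definition requires CD45-positive. The intersection is empty and the count is zero for every patient at every visit.

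2. **Activated definition applied alone.** The cells kept are CD45+, P1H12+, CD31+, CD34+, (CD105+ or CD106+) and CD133−. All are haematopoietic by the protocol's own use of CD45. Every cell with the same profile but CD45-negative is dropped.

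3. **Overlap with the consistent definition.** The population that fits the rest of the section is CD45−, P1H12+, CD31+, CD34+, (CD105+ or CD106+) and CD133−. A cell is either CD45-positive or CD45-negative, so this population shares no cell with the one in step 2. Under neither reading does the written definition count a single cell that the consistent definition would count.

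4. **Which sign fits the structure.** Having both CD105 and CD106 negative, and having at least one positive, are complementary conditions. With CD45-negative in both definitions, resting and activated CECs divide the CD45−, P1H12+, CD31+, CD34+, CD133− cells completely, with no overlap and no remainder. With the plus as written, the CD45-negative cells that carry an activation marker belong to neither class. This supports the minus as the intended sign.

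**The case against.** **The sign may be a conversion error.** The point rests on one superscript, and superscripts elsewhere in the section look damaged: the antibody list shows P1H followed by superscript 13,14, whereas both definitions name P1H12. The minus on CD133 in the same line shows that the text can carry both signs, but not that the CD45 sign was read correctly. This stands as a limit. The text available says CD45-positive, and only the source page can settle whether the protocol does.

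**The intended rule is already in the prose.** The exclusion sentence covers activated as well as resting cells, and a competent laboratory would probably see the slip. That is fair, and it makes a typographical error the likely explanation. It does not remove the contradiction: the itemised definition is the one a laboratory would copy into its gating template, and the protocol gives no other written profile for activated CECs.

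**The reach is limited.** Section 5.1 relies on CEC/CEP correlations in general and does not single out activated CECs, and section 13.1 calls the analysis exploratory. This stands.

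**A stronger reading that the documents do not support.** Section 2.1.1 reports a strong relation between vinorelbine AUC and falls in leucocytes or PMN. A reader might infer that a CD45-positive count would track leucocytes, fall with dose, and let myelosuppression pass for an anti-angiogenic effect. Three things stand against this:

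- The written definition also requires P1H12, CD31, CD34 and CD105 or CD106, and nothing in the documents shows that this narrow subset follows total leucocytes.
- Samples are mostly taken before a cycle, and the product information in 2.1.1 delays dosing until neutrophils recover, so they tend to fall at recovery rather than nadir. The argument is weaker for the metronomic schedule, which is dosed in every week of the cycle, but that does not establish a direction.
- If the exclusion is applied first, the count is zero throughout and shows no trend at all.

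**Conclusion.** The contradiction is real in the text at hand and lies within one section. As written, the activated-CEC definition selects either nothing or only CD45-positive cells bearing the endothelial and activation markers, so the activated-CEC readout is not valid.

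One component of the CEC/CEP secondary objective and of the metronomic dose determination is affected. The resting-CEC definition and the primary MTD endpoint are not. The protocol gives no cell counts, so the size and direction of any bias cannot be determined, and it would be wrong to say that the count tracks leucocytes or falls spuriously with dose.

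The conclusion assumes that the plus on CD45 is on the source page and is not a product of the conversion. If the page shows a minus, the definitions agree and only the check of the laboratory template remains.

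**What to change.** 1. Check the CD45 sign in the activated-CEC definition against the source page of section 9.1.1.
2. If the page also shows a plus, change the definition to CD45-negative, to match the exclusion step and the resting-CEC definition.
3. Confirm that the laboratory's gating template uses CD45-negative for activated CECs. If samples have already been analysed, establish which definition was applied to them.

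The cost is one character in section 9.1.1 and a check of the template. No extra samples or visits are needed, and nothing in the dose-escalation rules changes.
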